### Participants

Participants will be recruited locally (Maryland, District of Columbia, Virginia; USA) via mailings to selected physicians, announcements in newsletters, contacts with support groups and approved websites, advertisements and animated videos on social media, flyers and ads in public settings, and targeted mailings to households with children. We will follow n=40 youth (all genders; ages 8-17) over 6 in-person exposure sessions as part of a multiple-baseline trial of 12 weeks of exposure-based CBT for youth with clinically impairing irritability [73]. All participants and their legal guardians will provide informed assent (youth)/consent (parents/guardians). Eligible youth will be English-speaking, willing and able to provide informed assent with parental/caregiving informed consent, and present with at least one of two core symptoms of DMDD: abnormal mood or increased reactivity to negative emotional stimuli, with severe impairment in one domain (home, school, peers) and at least mild impairment in another, or moderate impairment in at least two domains [73]. Given the transdiagnostic nature of irritability, participants may have a primary diagnosis or comorbid diagnoses of DMDD, oppositional defiant disorder (ODD), ADHD, anxiety disorder(s), or other related disorders. Symptoms and diagnoses for inclusion and exclusion criteria will be established using the Kiddie-Schedule for Affective Disorders and Schizophrenia Present and Lifetime Version [45] with the additional DMDD supplement. Exclusion criteria include: (1) meeting current or past criteria for bipolar I/II disorder or any psychotic disorder; (2) persistent depressive disorder or current major depressive episode, PTSD, autism spectrum disorders (assessed using the Development and Well-Being Assessment [27], the Social Responsiveness Scale [18], the Social Communication Questionnaire [84], and the Children’s Communication Checklist-Second Edition [8, 76]; (3) IQ less than 70 as assessed by the Wechsler Abbreviated Scale of Intelligence (WASI; Vocabulary and Matrix Reasoning Scales) [106]; (4) a significant general medical or neurological condition; (5) meeting criteria for alcohol or substance use disorder within the last three months; and (6) conditions or life situations that would interfere with the participant’s ability to participate in treatment. Participants with past major depressive disorder will not be excluded. Given the parameters of the overarching clinical trial, participants taking medications (e.g., serotonin-selective reuptake inhibitors, anticholinergics, amphetamines, allergy medications, etc.) that could impact cardiovascular and electrodermal activity will not be excluded. Rather, medication use will be considered as a candidate covariate in analyses. Enrolled participants’ medications (if any) will be written by a psychiatrist at the National Institute of Mental Health working with the study team, and no changes in medication will occur during treatment unless there is an acute clinical need. Eligible consented participants will be randomized to a staggered start schedule as part of the multiple-baseline design, with either a two-, four-, or six-week baseline period. All study visits will occur at a single site, at the National Institute of Mental Health in Bethesda, MD.

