
### Study design

The data for the present study come from a randomized multiple baseline trial of exposure-based CBT. Each participant is randomized to 2, 4, or 6 weeks of baseline observation prior to treatment beginning. This design controls for the effects of time and regression towards the mean. Randomization is performed in blocks of 10 participants with a 1:1 within-block ratio. The assignment sequence was created via a computer-based random number generator. Clinicians conducting assessments (see below) are blinded to the trial phase from commencement of the baseline period, and the blind will not be broken for the entire cohort until the completion of the trial. The exposure-based CBT protocol will consist of twelve weekly sessions. Sessions are administered by two expert clinical psychologists. In-person exposure sessions (~30-45 minutes) will occur at weeks 5-10 in the protocol. Peripheral psychophysiological data will be collected during these six in-person exposure sessions. The main outcomes we plan to assess are changes in HR, HRV, and EDA over the course of exposure sessions and relations between changes in psychophysiological data and clinical symptoms. Clinical symptoms will be assessed weekly by clinician raters, including at mid-treatment, post-treatment, and 3- and 6-months post-treatment follow-up. Group supervision is conducted by the treatment developer and clinicians rate themselves on adherence after each session in order to improve adherence and minimize drift. Patients who request to discontinue or whose condition worsens (as determined by the clinical team and PI) may meet criteria for discontinuation. All participants are informed of their ability to discontinue at any time for any reason without the loss of benefits to which they are other entitled. For more extensive details regarding the intervention, please see Naim et al., 2021 and [69].

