### Data analysis

Extensive details of data management procedures can be found in Naim et al., 2021 and [69]. All participant data is de-identified using a numeric code to ensure confidentiality before, during, and after the trial. Only approved staff at the study site (National Institute of Mental Health) will have access to data. Estimates for HR, HRV, and EDA will be calculated as the session average for each individual across all sessions. Given the tendency of physiological data to be non-normally distributed, we will log-transform HR, HRV, and EDA data as necessary [55]. Questionnaire data will also be screened for normality and univariate outliers.

Multilevel models will be fit. Sessions (time; level 1) will be nested within person (level 2). Psychophysiological variables (HR, HRV, and EDA) from session 1 will be included at both levels 1 and 2 to account for the effects of individual differences at baseline on the intercept and slope, allowing us to test whether individual differences are predictive of treatment response within this model. Linear, quadratic, and cubic fits will be compared to determine the best-fitting model of change over treatment. First, we will sequentially fit models with psychophysiological indicators (HR, HRV, or EDA) from each of the five in-person exposure sessions defined as the outcome variable to assess change over time. Second, we will model severity of irritability based on the CGI as the outcome variable, and psychophysiological variables will be grand mean centered and entered as predictors at level 2 to assess the relation between change in psychophysiological parameters over time and irritability at post-treatment, 3-month follow-up, and 6-month follow-up. Missing data will be assessed for systematic loss and will be handled using full information maximum likelihood, which can handle both missing data and unequal time between measurement intervals [38]. We will use the Bonferroni-Holm method to correct for multiple comparisons.

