In addition to the dimensional models described above, wherein irritability and change in irritability are conceptualized continuously, we will also fit dichotomous treatment response models. Individuals will be classified as either high or low responders per the methodology described in [60]. High responders will be defined as those individuals who demonstrate a 50% or greater reduction in irritability based on the CGI at post-treatment assessment. Multilevel models will be fit as described above, with responder status as the outcome variable.

Should our primary hypothesis testing reveal changes in arousal (HR/EDA) and regulation (HRV) over the course of in-person exposure sessions, we will perform post hoc exploratory analyses to investigate the temporal relationship between psychophysiology and change in symptoms over the course of treatment using cross-lagged panel modeling. To capture weekly variation in symptoms, we will use the CGI rated at each exposure session. A random intercept cross-lagged panel model (RI-CLPM) will be specified in R using the lavaan package [82]. Four components will be specified: (1) a between component, consisting of random intercepts; (2) within-person fluctuations; (3) the lagged regressions between within-person components; and (4) covariances of the within and between components [68]. Within-person variables will be mean-centered.

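### Responder status is one value per child, yet the article makes it the outcome of a sessions-within-person multilevel model, in which it cannot vary at level 1

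*Protocol article*

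**What the plan says.** All of this is in the Data analysis section of the protocol article, unless another section is named.

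- **Model structure:** "Sessions (time; level 1) will be nested within person (level 2"). Linear, quadratic and cubic change over time are to be compared.
- **Physiology in the CGI model:** "psychophysiological variables will be grand mean centered and entered as predictors at level 2".
- **Responder definition:** "High responders will be defined as those individuals who demonstrate a 50% or greater reduction in irritability based on the CGI at post-treatment assessment". The unit classified is the individual, and there is one classification time.
- **Responder model:** "Multilevel models will be fit as described above, with responder status as the outcome variable".
- **Number of rows:** the Participants section gives 40 youth and six exposure sessions, and Study design agrees ("Peripheral psychophysiological data will be collected during these six in-person exposure sessions"). Data analysis instead refers to data "from each of the five in-person exposure sessions defined as the outcome variable to assess change over time". The point here is the same for five or six.

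The responder analysis is introduced as an addition to the continuous models. The article gives no link function, no random-effects structure beyond the nesting, and no person-level model for it.

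**The concern.** A two-level model separates variation between children from variation between sessions within a child. Responder status is a property of the child, so every session row of a child carries the same value and the within-child part is empty. The model that the sentence calls up is therefore mismatched to its outcome.

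The article presents prediction of treatment response as an aim, and this is its only analysis that contrasts high with low responders. If it cannot be run as written, a replacement will have to be chosen once the data are in hand, with at most 40 binary outcomes. One easy replacement, treating session rows as independent, would greatly overstate the evidence.

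**Working it through.** The article states no figure for the responder model, so there is none to reproduce. The powers under Sample size and power analysis are for hypotheses 1, 2 and 4 and do not bear on this.

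**Inputs.** From the article: n = 40 children, k = 6 or 5 sessions, one binary value per child, alpha 0.05. Assumed: two-sided testing, a logit link with a normal random intercept, 40% or 50% responders, and intraclass correlation (ICC) of session physiology 0.3, 0.5 or 0.7.

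**Step 1. Random-intercept logistic likelihood.** Let Z be standard normal and p = expit(b + SD·Z). A responder contributes L1 = E[p^k] and a non-responder L0 = E[(1-p)^k]. With r responders, the log-likelihood is r·ln L1 + (n-r)·ln L0.

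For 0 < p < 1 and k ≥ 2, p^k + (1-p)^k < 1, so L1 + L0 < 1 at any finite SD. The log-likelihood therefore stays strictly below r·ln(r/n) + (n-r)·ln(1-r/n). It approaches that bound only as SD grows without limit, so there is no finite maximum.

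Maximising over b at fixed SD:

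- 20/40 responders, k = 6: -139.4, -70.8, -37.7, -28.9 at SD 0.5, 2, 8, 64. Bound: 40·ln 0.5 = -27.7.
- 16/40 responders, k = 6: -102.2, -43.0, -34.5 at SD 1, 5, 10. Bound: 16·ln 0.4 + 24·ln 0.6 = -26.9.
- 16/40 responders, k = 5: -91.2, -41.3, -33.8 at SD 1, 5, 10. Same bound.

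**Step 2. Effect on the slope.** In one simulated data set with a person-level predictor (k = 6), the fitted slope was 0.80, 1.16, 2.21 and about 4 at SD 1, 2, 5 and 10. As odds ratios, exp(0.80) = 2.2 and exp(2.21) = 9.1. The same 40 children analysed with one row each gave a slope of 0.57 (SE 0.42), which is finite and stable.

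**Step 3. Linear mixed model on the same kind of data.** The residual variance collapsed to about 3e-12. The time coefficient (about 1e-14) and the session-level physiology coefficient (about 1e-12) were forced to zero. Linear, quadratic and cubic time terms have nothing to describe.

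**Step 4. If the person level were dropped.** This departs from the plan. For a person-level predictor copied over k rows, standard errors are too small by √k: √6 = 2.45. The expected null rejection rate is 2·(1 - Φ(1.96/√6)) = 42%, or 38% with k = 5. Simulated null rejection rates, 40% responders, about 2,000 runs per setting:

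| k | ICC | Pooled, session-level predictor | Pooled, person mean | Pooled, cluster-robust (session-level predictor) | One row per child (person mean) |
|---|---|---|---|---|---|
| 5 | 0.3 | 0.184 | 0.391 | 0.058 | 0.040 |
| 5 | 0.5 | 0.251 | 0.384 | 0.050 | 0.034 |
| 5 | 0.7 | 0.329 | 0.395 | 0.063 | 0.048 |
| 6 | 0.3 | 0.253 | 0.473 | 0.064 | 0.041 |
| 6 | 0.5 | 0.290 | 0.423 | 0.059 | 0.041 |
| 6 | 0.7 | 0.336 | 0.415 | 0.050 | 0.034 |

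**Step 5. Other readings of the sentence.** Taking post-treatment, 3-month and 6-month rows, as in the CGI model, leaves the outcome constant, because status is defined at post-treatment only. Placing physiology at level 2 changes the predictor and not the outcome.

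**The case against.** - **False-positive rates above 40%.** A reader might infer that the plan as written carries them. It does not. The article keeps the person level; the inflation needs an analyst to discard it and treat about 240 rows (40 × 6) as independent. Even then, rates above 40% arise mainly when a person-level predictor is copied over six rows. With session-varying physiology they were 18-34%. Cluster-robust errors kept the rate at 5-6%, though the article does not plan them. An analyst meeting non-convergence could equally collapse to one row per child.
- **No two-level model could work.** A reader might also infer this, but it goes too far. A multilevel structural equation model can predict a person-level outcome from the random intercepts and slopes of session physiology, and full information maximum likelihood is compatible with that. The article does not name such a model for responder status: lavaan appears only for the cross-lagged analysis, and the sentence refers back to the sessions-within-person models. The objection limits the fault to the conventional reading but does not remove it.
- **Condensed article.** Link function and random effects may well be set out in a fuller plan, so their absence is not the fault. The fault is in the pairing of outcome and model that the article does state.
- **Reach.** The primary hypotheses rest on models with physiology or continuous CGI as outcome. This part of the objection stands in full and lowers the severity.

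**Conclusion.** The point holds in a limited form. Read conventionally, the responder model has an outcome with no within-child variation, no finite estimate of the intercept variance, odds ratios that depend on where fitting stops, and time terms with nothing to fit. This follows from the definitions and does not depend on the assumed responder rate, the ICC, or five versus six sessions.

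The 18-47% null rejection range is conditional. It applies only if session rows are pooled without their clustering, and it moves with the ICC, the number of rows and whether the predictor varies by session. It was simulated at 40% responders; a separate run at 50% with six rows and a person-level predictor gave 43%, inside the range.

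The fault is confined to the additional dichotomous analysis. It should be corrected, but it does not touch the primary hypothesis tests, the sample size or the data collection.

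**What to change.** Replace the sentence on the responder model with a single-level logistic regression, one row per participant. The outcome is responder status and the predictors are person-level physiology: the session-1 value and the person's slope over the exposure sessions. Keep the predictors few, since there are at most 40 outcomes; penalisation is optional. In the checks above, one-row logistic regression on the person mean held the null rejection rate at 3-5%.

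A multilevel model with physiology as the level-1 outcome, and responder status and session × responder status as predictors, may be added as a complement. The text should then say that it tests whether responders differ in physiology, not whether physiology predicts response, so it does not replace the first model.

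The cost is a change of analysis wording. No data collection or sample size changes.

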## Discussion

This study protocol tests peripheral psychophysiological mechanisms that may underly exposure-based CBT for youth with clinically impairing irritability. The current protocol leverages state-of-the-art measures by collecting ambulatory psychophysiological data in the context of treatment via a medical-grade device. Psychophysiological data will be evaluated alongside intensive, weekly clinical ratings from patients, parents, and trained clinicians. Despite the strengths and innovative aspects of the current study, the multiple-baseline trial is not a randomized controlled trial; therefore, it does not allow for strong causal inferences.

In-session measurement of psychophysiology over the course of treatment could provide a more nuanced understanding of mechanisms underlying exposure-based CBT for clinically impairing irritability, as well as predictors of treatment outcomes [108].

## Data Availability

We plan to share datasets and scripts from the study described herein in a publically accessibly database; at this time data sharing is not applicable as no data is described herein. Study findings will be disseminated through publications in peer-reviewed journals, presentations at national and international conferences, presentations to local community partners (e.g., school districts, parent-teacher associations, community providers, and advocacy organizations), on the lab’s website, and through a quarterly newsletter distributed to lab member and study participants.

## Abbreviations

CBT: Cognitive behavioral therapy
HR: Heart rate
EDA: Electrodermal activity
HRV: Heart rate variability
BVP: Blood volume pulse
CGI: Clinical Global Impressions Scale
ARI: Affective Reactivity Index
NIMH: National Institute of Mental Health
ADHD: Attention-deficit/hyperactivity disorder
DMDD: Disruptive mood dysregulation disorder
DSM: Diagnostic and Statistical Manual
ANS: Autonomic nervous system
vmPFC: Ventromedial prefrontal cortex
SNS: Sympathetic nervous system
PE: Prolonged exposure
PTSD: Posttraumatic stress disorder
RMSSD: Root mean square of successive differences
BOLD: Blood oxygen level-dependent
SDNN: Standard deviation of the normal to normal beat interval
USA: United States of America
ODD: Oppositional Defiant Disorder
WASI: Wechsler Abbreviated Scale of Intelligence
CL-ARI: Clinician Affective Reactivity Index
CGI-S: Clinical Global Impressions-Severity
CGI-I: Clinical Global Impressions-Improvement
PPG: Photoplethysmography
IBI: Inter-beat interval
RR: Successive R waves
SA: Sinoatrial
ECG: Electrocardiogram
RI-CLPM: Random intercept cross-lagged panel model
